### Sample size

2.13

Sample size was calculated using PASS 15.0 software. The primary outcome measure was ALT level on postoperative day 2. Preliminary data showed a mean ALT level of 249.8 ± 147.9 U/L after partial hepatectomy. In a pre-experimental phase, taVNS interventions reduced ALT to 174.9 ± 103.5 U/L (approximately 30% reduction). With a significance level (*α*) of 0.05 and statistical power (1 − *β*) of 90%, a two-sided test determined a minimum sample size of 63 participants per group. Accounting for a 10% potential dropout rate, we plan to recruit 140 patients and randomly allocate them to active-taVNS and sham taVNS groups. Regarding the validation of the Minimal Clinically Important Difference (MCID), we estimated the MCID using a stepwise approach based on previous research methods (44). In this experiment, the sham taVNS group’s mean ALT ± standard deviation on postoperative day 2 was 249.8 ± 147.9 U/L, while the active-taVNS group was 174.9 ± 103.5 U/L, with a pooled standard deviation of 127.64. Conventionally, the MCID range is typically set between 0.2 and 0.5 times the pooled standard deviation, resulting in a reasonable MCID interval of 25.53 to 63.82. The mean difference between groups (*Δ*) was 74.9. When the intergroup difference exceeds the upper limit of the MCID, it indicates that the observed effect difference has clinical significance, thus supporting the reasonableness of the MCID determination.

### Statistical analysis

2.14

Statistical analyses will be performed using SPSS software (version 27.0; IBM) and statistical charts will be generated with GraphPad Prism (version 8.0). Normality of data will be assessed using the Kolmogorov–Smirnov test, and variance homogeneity will be evaluated by the Levene test. Normally distributed continuous data will be presented as mean ± standard deviation, while non-normally distributed data will be reported as median with interquartile range.

Statistical analyses will employ independent samples t-tests for normally distributed continuous data and Mann–Whitney U tests for non-normally distributed data. Time-to-event outcomes will be evaluated using Kaplan–Meier curves and Log-rank tests. Multivariate analyses will utilize multiple linear or logistic regression models based on dependent variable type. Repeated measures data will be analyzed using generalized estimating equations. The analysis will follow the intention-to-treat principle, with multiple imputation addressing missing data the per-protocol Analysis will be included as part of the sensitivity analysis. A significance level of *α* = 0.05 will be applied, with *p* < 0.05 considered statistically significant.

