#### Primary outcome

2.10.1

The primary endpoint is serum alanine aminotransferase (ALT) levels on postoperative day 2. Perioperative hepatic injury occurs in two distinct phases. The first phase, occurring 2–6 h after reperfusion, is characterized by Kupffer cell-induced oxidative stress and the initiation of cell necrosis and apoptosis. The second phase, spanning 6–48 h after reperfusion, involves inflammatory cell aggregation in the hepatic microvascular system, including sinusoids and post-sinusoidal regions, accompanied by sinusoidal congestion, neutrophil adhesion leading to blood flow obstruction, and inflammatory cell extravasation into the hepatic parenchyma (31, 32). Furthermore, evidence indicates that intermittent stimulation effectively alleviates patient discomfort and improves treatment safety (33). Based on these pathological mechanisms, we implemented taVNS intervention throughout the entire hepatic injury inflammatory response to maximize inflammation mitigation and minimize hepatic damage. Liver injury severity is classified as follows: ① Mild acute liver injury (ALI) is typically defined as 2 × upper limit of normal (ULN) ≤ ALT < 5 ULN; ② Moderate ALI is typically defined as 5 ULN ≤ ALT < 15 ULN; ③ Severe ALI requires: International Normalized Ratio (INR) ≥ 2.0, ALT ≥ 10 ULN, serum total bilirubin (TBiL) ≥ 3.0 mg/dL, and absence of hepatic encephalopathy (34–36). Baseline venous blood samples will be obtained during the preoperative anesthesia visit after obtaining informed consent (t0). The primary endpoint will be venous blood samples collected at 7:00 AM on the second postoperative day (t4) after stimulation cessation.

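### Section 2.14 lets a normality test on the trial data choose the primary ALT test, so test and estimand are not fixed in advance and baseline ALT goes unused

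*Protocol article*

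**What the plan says.** Section 2.10.1 of the protocol article defines the endpoint: "The primary endpoint is serum alanine aminotransferase (ALT) levels on postoperative day 2". It also provides for a baseline sample: "Baseline venous blood samples will be obtained during the preoperative anesthesia visit after obtaining informed consent (t0"), and Table 1 lists ALT at t0, t4 and t6.

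Section 2.14 sets the analysis. It begins with "Normality of data will be assessed using the Kolmogorov–Smirnov test, and variance homogeneity will be evaluated by the Levene test" and continues with "Statistical analyses will employ independent samples t-tests for normally distributed continuous data and Mann–Whitney U tests for non-normally distributed data". Multiple regression and generalized estimating equations are also mentioned, but without naming an outcome or covariates, so neither is assigned to day-2 ALT.

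Section 2.13 sizes the trial on a difference in raw means. The control figure is given as "Preliminary data showed a mean ALT level of 249.8 ± 147.9 U/L after partial hepatectomy", and the active figure as "taVNS interventions reduced ALT to 174.9 ± 103.5 U/L (approximately 30% reduction"). The MCID interval of 25.53 to 63.82 U/L is 0.2 to 0.5 times the pooled SD of 127.64.

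**The concern.** Until the outcome data have been tested for normality, nobody can say which test is primary or what effect it estimates. The t-test compares mean ALT, the scale of the sample size and the MCID. Under the Mann-Whitney branch the section reports medians and interquartile ranges and names no effect estimate to set against that MCID. Section 2.14 does not say which version of the Kolmogorov-Smirnov test applies, or whether it is run per arm, and these choices can change the branch taken.

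Both branches are also unadjusted. Baseline ALT is measured before surgery in every patient, and section 2.6 describes no stratification. A chance imbalance in baseline ALT would therefore stay in the primary comparison, and any precision the baseline offers would be lost.

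**Working it through.** **Inputs (section 2.13).** Control 249.8, SD 147.9; active 174.9, SD 103.5; two-sided alpha 0.05; power 90%; dropout 10%.

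**1. The plan's own figure.**
- Pooled SD = √((147.9² + 103.5²)/2) = 127.65 (stated: 127.64). Difference = 249.8 − 174.9 = 74.9. Standardised effect = 74.9/127.65 = 0.587.
- Normal approximation: n = 2(1.960 + 1.282)²/0.587², which gives 62 per arm. The exact t calculation gives 63, with power 90.5%.
- 63/0.90 = 70 per arm, or 140. The stated size reproduces.

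**2. What these figures imply about shape.**
- Mean minus 2 SD: 249.8 − 295.8 = −46.0 and 174.9 − 207.0 = −32.1. A normal model puts Φ(−249.8/147.9) = 4.6% of values below zero. Normality is implausible and ALT is probably right-skewed.
- Coefficient of variation: 147.9/249.8 = 0.592 and 103.5/174.9 = 0.592. The ratio of means is 0.700.

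**3. Which branch is taken (simulation, 63 per arm, the plan's means and SDs).**
- Lognormal shape: the Kolmogorov-Smirnov test corrected for estimated parameters rejects normality in at least one arm in 98% of trials; the uncorrected version in about 41%.
- Gamma shape: the corrected version rejects in about 87%.
- Under the lognormal alternative, the t-test and Mann-Whitney disagree on significance in about 5% of trials.
- The target differs too. Under the lognormal model the medians are 214.9 and 150.5, a difference of 64.4 U/L, against 74.9 for the means.

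**4. Type I error.** The planned rule with the corrected version gives 4.8 to 5.3%. With the uncorrected version it is about 5.7% (lognormal). Log-scale ANCOVA gives 4.8 to 5.3%.

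**5. Power of the planned rule against log-scale ANCOVA.** For the lognormal model, log SD = √ln(1 + 0.592²) = 0.548, log difference = 0.356, and standardised effect = 0.356/0.548 = 0.650. The table uses 20,000 simulated trials per row and the corrected Kolmogorov-Smirnov test. Here r is the correlation of the baseline covariate with day-2 ALT. It is assumed, because the documents do not give it.

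| Shape | r | Planned rule | Log ANCOVA | Difference (points) |
|---|---|---|---|---|
| Lognormal | 0 | 94.0% | 94.8% | +0.8 |
| Lognormal | 0.3 | 94.1% | 96.4% | +2.3 |
| Lognormal | 0.5 | 94.2% | 98.6% | +4.4 |
| Gamma | 0 | 88.5% | 86.4% | −2.1 |
| Gamma | 0.3 | 88.1% | 88.9% | +0.8 |
| Gamma | 0.5 | 88.2% | 94.0% | +5.8 |

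A separate simulation put the gamma loss at r = 0 nearer 2.5 points.

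The least favourable case for ANCOVA is a gamma shape with the t-test branch taken. The t-test then has 92.1%, 91.4% and 91.4% power at r = 0, 0.3 and 0.5, so ANCOVA differs by −5.7, −2.5 and +2.6 points.

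**The case against.** The strongest reply is that nothing here threatens validity. Unadjusted comparison in a randomised trial is unbiased, type I error stays close to 5%, and the sample size is right. Covariate lists are commonly left to an analysis plan, which is not shown. All of that stands, except that the point does not rest on missing detail: section 2.14 states a rule, and the rule leaves the primary test open.

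Four further objections limit the case:

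- **Power.** A reader might set 95.2% (log-scale t-test) against 90.5% (raw t-test) and read the difference as the gain. That is the wrong comparator, because under a lognormal shape the planned rule mostly ends in Mann-Whitney, at about 94%.
- **Scale.** Equal coefficients of variation might be read as proof of a multiplicative effect. But 0.7 × 249.8 = 174.86 and 0.7 × 147.9 = 103.53, so the active-arm figures equal 0.7 times control to rounding. They would look the same if they had been scaled as a planning assumption, and they fit a gamma shape as well as a lognormal one.
- **Units.** A ratio of geometric means is not on the U/L scale of the MCID either, and Mann-Whitney can be accompanied by a Hodges-Lehmann shift in U/L. The ratio therefore needs a U/L difference beside it.
- **Covariates.** It is tempting to say that everything needed is already collected. Baseline ALT is, and diagnosis follows from eligibility (section 2.3). Major or minor extent is not shown to be: section 2.12 defines it under intraoperative data, and the preoperative list has only an undefined surgical type.

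**Conclusion.** The concern holds as a matter of specification and efficiency. The primary test and its effect measure depend on a pre-test of the outcome data, and a baseline measured in every patient is not used. A single baseline-adjusted analysis is better and nearly free.

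The documents do not support reading this as an underpowered trial or an inflated error rate. Nor do they support a guaranteed power gain. Against the planned rule with the corrected normality test, the change is about +1, +2 and +4 to 5 points (lognormal) or about −2.5, +1 and +6 points (gamma) at r = 0, 0.3 and 0.5. Both shape and r are assumptions. The main reason for the change is a fixed test and estimand; power is a conditional benefit.

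**What to change.** In section 2.14, name one primary analysis: ANCOVA of log day-2 ALT on arm and log baseline ALT (t0), with diagnosis (cancer or hemangioma) as a further pre-surgery covariate.

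- Report the ratio of geometric means with 95% CI, which matches the proportional reduction in section 2.13. Give the difference in U/L as well, so that it can be read against the MCID.
- Drop the normality pre-test for the primary endpoint and keep Mann-Whitney as a sensitivity analysis.
- Add planned resection extent only if it is recorded before surgery. Do not adjust for extent as found at operation.

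The cost is wording, to be fixed before anyone sees outcomes by arm. Baseline ALT and diagnosis need no new data, and the model is within reach of the software named. The downside is that the primary effect becomes a ratio instead of a raw difference, and some power may be lost if baseline ALT predicts little and ALT is not close to lognormal.

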## Discussion

3

Partial hepatectomy remains the primary surgical treatment for primary and metastatic liver tumors (5). However, several perioperative risk factors can negatively affect liver function. From an anatomical and physiological perspective, the separation of liver parenchyma results in substantial microscopic and organ-level alterations in perfusion, directly impacting the liver’s blood supply and drainage system (8). Massive intraoperative blood loss may trigger fluid redistribution and systemic inflammatory responses, thereby substantially increasing the risk of postoperative infections (45, 46). Moreover, evidence suggests that extensive hepatectomy and the presence of hepatocellular carcinoma are key risk factors for postoperative coagulopathy and the development of a hypercoagulable state (47). Although the Pringle maneuver is commonly employed for intermittent occlusion of the portal vein to control intraoperative bleeding, prolonged occlusion may exacerbate HIRI and further impair liver function (48). Studies have shown that HIRI can lead to liver failure and systemic inflammatory response syndrome (SIRS), which may reduce postoperative tumor-free survival rates and elevate the risk of tumor recurrence (9, 49, 50). Furthermore, preclinical studies have demonstrated that chronic stress negatively affects liver regeneration and is associated with increases mortality following partial hepatectomy in mice (51). These findings are corroborated by population-based studies, which show that elevated levels of psychological stress are linked to higher mortality rates among patients with liver disease (52). Perioperative liver protection has therefore emerged as a key area of focus in the fields of in anesthesiology and surgical practice. Traditional hepatoprotective strategies during the perioperative period include ischemic preconditioning and anesthetic preconditioning. Although clinical evidence suggests that ischemic preconditioning can significantly reduce postoperative transaminase levels, its clinical applicability is limited by the complexity of the procedure, which involves repeated clamping of the portal vein and may potentially cause damage to small portal vein branches (53). A recent meta-analysis challenges the efficacy of ischemic preconditioning in reducing liver damage caused by ischemia–reperfusion injury during hepatectomy, thereby challenging its hepatoprotective benefits in the perioperative setting (12). The hepatoprotective effects of propofol remain a subject of debate. Although certain studies suggest that propofol anesthesia may significantly reduce postoperative ALT levels and decrease the incidence of complications, a meta-analysis has also identified a potential link between propofol and drug-induced liver injury (54, 55). Opioids have shown promise in ameliorating hepatic ischemia–reperfusion injury through their anti-inflammatory properties and modulation of vagal nerve activity. However, their use is accompanied by a risk of respiratory depression, which warrants cautious application in clinical practice (56). taVNS, as a novel perioperative strategy for liver protection, is characterized by its notable for its ease of application, minimal side effects, and well-established theoretical basis. VNS has been confirmed to attenuate perioperative hepatic injury through several mechanisms, including upregulation of *α*-7nAChR expression, activation of the CAP, and elevation of glutathione levels (19–21). Recent studies have indicated that vagal hepatic branches play a crucial role in promoting liver regeneration. Liu et al. demonstrated that activation of vagus nerve enhances IL-6 signaling in hepatic macrophages, thereby promoting hepatocyte proliferation and regeneration (57). Moreover, VNS has exhibited promising potential in suppressing tumor growth and metastasis. In a mouse model of colorectal cancer with liver metastasis, selective deactivation of the vagus nerve was associated with a significant increase in the number of hepatic metastatic nodules, higher mortality rates, and larger tumor volumes compared to those observed in the sham-operated group (58). Finally, research indicates that VNS can induce the release of acetylcholine (Ach) through the spleen, which subsequently interacts with the *α*-7nAChR on T lymphocytes and platelets, thereby promoting calcium ion influx, enhancing α-granule release, and activating circulating platelets to increase local thrombin generation. As a result, this mechanism accelerates the coagulation cascade and reduces hemorrhage at the site of tissue injury, thereby improving patient recovery outcomes (59). These findings suggest that VNS may function as a comprehensive, multidimensional perioperative strategy for hepatoprotection, capable of attenuating hepatic injury, decreasing perioperative blood loss, suppressing tumor progression, and facilitating liver regeneration. In terms of safety, a systematic review of available literature on taVNS, not restricted to cardiovascular applications, revealed that the most frequently reported adverse events were localized stimulation-related symptoms such as pricking sensations, pain, swelling, or itching, occurring in 16.7% of cases. Additional adverse events included headache (3.3%), nasopharyngitis (1.6%), and dizziness or syncope (1.4%). Importantly, only three serious adverse events were considered directly attributable to taVNS (60). VNS primarily comprises two modalities: implanted VNS (iVNS) and transcutaneous VNS (tVNS). The latter includes both taVNS and transcutaneous cervical VNS (61). iVNS is associated with potential complications such as delayed bradycardia, severe cardiac arrest, including bradycardia, peritracheal hematoma, and atrioventricular block. Furthermore, its clinical application is significantly constrained by high implantation costs (62–64). Due to its favorable safety profile, low cost, and ease of access, taVNS has increasingly been considered a promising first-line therapeutic option (65). Previous clinical studies have demonstrated that non-invasive VNS exhibits efficacy comparable to that of traditional implantable VNS (66).

Currently, both clinical practice and scientific research predominantly focus on individual diseases or physiological systems. However, the prevailing disease-oriented diagnostic and therapeutic paradigm requires urgent reevaluation (67). Complex comorbidities involving central and peripheral systems are common in clinical settings, often interacting in ways that exacerbate and accelerate disease progression (67). A growing body of evidence indicates that perioperative factors, such as anxiety, preoperative fasting, and postoperative pain, can negatively influence surgical outcomes and contribute to increased mortality among patients with liver disease (52, 68, 69). Moreover, the prevalence of depression is significantly elevated in individuals with chronic liver disease. Hepatic injury induced by ischemia–reperfusion during partial hepatectomy can lead to systemic inflammation, which may in turn trigger depressive-like phenotypes (70). In a 2024 review titled “Transcutaneous auricular Vagus Nerve Stimulation as a Novel Therapy Connecting Central and Peripheral Systems,” it was highlighted that taVNS therapy is widely utilized in the regulation of central nervous system disorders, including epilepsy, depression, insomnia, migraine, anxiety, phobia, cognitive impairment, post-traumatic stress disorder, Parkinson’s disease, disorders of consciousness, and cognitive decline (71, 72). Furthermore, taVNS has been shown to modulate the function of peripheral organs, including the heart, lungs, liver, pancreas, gastrointestinal tract, and spleen (67). Consequently, taVNS therapy presents a promising therapeutic approach for conditions arising from autonomic dysfunction in both central and peripheral nervous systems, providing a novel strategy for addressing comorbidities (67).

ALT is a well-recognized biomarker for liver injury. Compared to AST, ALT exhibits higher specificity in identifying hepatocellular damage and is commonly included in standard metabolic panels as a key indicator of hepatic dysfunction. ALT activity primarily found in the cytoplasm of hepatocytes, where intracellular concentrations are approximately 3,000 times greater than those in the serum. As a result, both acute and chronic hepatocyte injury can significantly increase serum ALT levels due to the release of this enzyme from damaged or necrotic cells (73, 74). ALT has been widely utilized as a primary endpoint in numerous preclinical and clinical studies assessing interventions for liver injury. With a half-life of approximately 48 h and its relevance to the intervention period extending through postoperative day two, ALT serves as a suitable and reliable primary outcome measure for the present study (73, 75, 76).

In the absence of prior research on the hepatoprotective effects of taVNS, we determined our stimulation parameters based on preclinical evidence derived from traditional VNS studies (23). A systematic review of 33,531 taVNS-related studies indicated that 74% utilized a stimulation frequency of 20 Hz, with more than half employing a pulse width of 200 μs. Taking both safety and efficacy into account, we selected a stimulation protocol of 20 Hz and 200 μs (77).

Several limitations of this study should be acknowledged. First, as a single-center study with a relatively modest sample size, the generalizability of the findings may be limited. Second, the restricted variety of hepatectomy types and the limited number of liver transplant procedures conducted at our institution may constrain the broader applicability of the results. Concerning the intervention protocol, we applied fixed stimulation parameters without systematically investigating potential dose–response relationships across different parameter combinations. Finally, although we will assess levels of inflammatory cytokine such as IL-6 and TNF-*α*, we will not directly measure upstream indicators such as vagal nerve activity or α-7nAChR expression, thereby leaving the activation mechanism of the cholinergic anti-inflammatory pathway at a speculative level.

Although preclinical studies on taVNS for hepatic protection during the perioperative period are emerging, clinical evidence remains limited. This study examines the effect of this non-invasive neuromodulation technique on postoperative liver function in patients undergoing elective partial hepatectomy. By introducing this novel therapeutic approach, the research provides a new perspective on multimodal perioperative hepatoprotection and may contribute to the advancement of organ preservation strategies.

## Glossary

taVNS: Transcutaneous auricular vagus nerve stimulation
HIRI: Liver ischemia–reperfusion injury
VNS: Vagus nerve stimulation
iVNS: Vasive vagus nerve stimulation
*α*-7nAchR: Alpha-7-nikotinische Acetylcholinrezeptoren
CAP: Cholinergic anti-inflammatory pathway
TNF-α: Tumor necrosis factor-α
ALT: Alanine aminotransferase
AST: Aspartate aminotransferase
TBA: Total Bile Acid
DBIL: Direct Bilirubin
TBIL: Total Bilirubin
BUN: Blood Urea Nitrogen
Cr: Creatinine
IL-6: Interleukin-6
APTT: Partial thromboplastin time
PT: Prothrombin time
INR: International normalized ratio
SIRS: Systemic inflammatory response syndrome
BIS: Bispectral index
PACU: Post-anesthesia care unit
PCA: Patient-controlled analgesia
SAS: Simpson-Angus Scale
CAM: Confusion Assessment Method
FSS: Fatigue Severity Scale
NRS: Numerical Rating Scale
QoR-15: Quality of Recovery-15
FRAIL: Fatigue, Resistance, Ambulation, Illness and Loss of Weight Index
IEED: Intake, feeling nauseated, emesis, exam and duration of symptoms scoring system
SAEs: Serious adverse events
AEs: Adverse events
